#### 2.2.2 Healthy volunteers

A total of 40 healthy volunteers will be recruited. They must meet the following criteria: be aged 18 years or older, be able to speak and read French and sign a written informed consent before intervention procedure. They will be not included if they have: current or a history of psychiatric disorder (based on a structured interview with a trained psychiatrist), anosmia (as verified by the ETOC), a current pharmacological treatment, or contraindications to TMS.

### 2.3 Intervention

All stimulations for therapeutic intervention will be delivered using a MagPro X100 (MagVenture, Mag2Health, France) equipped with a 65 mm figure-of-eight coil with active cooling (MCF-Cool B65). Patients will be comfortably installed in a dedicated room for brain stimulation. During each session, the 3D T1-weighted images of all participants will be used for neuronavigation and the position and orientation of the coil will be monitored using a neuronavigation system (Syneika system, France).

At the first session, the primary motor cortex (M1) hand area will be located by identifying the optimal scalp sit (hotspot) that elicits the largest amplitude of motor evoked potentials (MEPs) in the right hand's first dorsal interosseus (FDI) muscle for a given intensity. The resting motor threshold (rMT) will then be established as the lowest stimulation intensity to evoke at least 5 MEP of 50 μV peak-to-peak amplitude from 10 consecutive (Rossini et al., 1994).

For the rTMS protocol, the coil will be positioned over the left DLPFC based on the individual anatomical T1-weighted MRI. The targeted left DLPFC will be identified based on a predefined identification by the Syneika neuronavigation system, i.e., the junction between areas BA9 and BA46, according to the algorithm proposed by Mylius et al. (2013). The exact same target will be maintained for each rTMS session to ensure precise and reproducible placement of the stimulation coil.

The rTMS protocol includes 50 sessions over 10 days (i.e., 5 sessions per working day, 1 h apart, for 2 weeks). Each session lasts 9min40 and involves 1,800 pulses at 90% rMT, delivered in bursts of 3 pulses at 50 Hz, repeated at 200 ms intervals for 2 s (i.e., at 5 Hz). This particular rTMS protocol is called intermittent theta-burst stimulation (iTBS). A 2-second train of iTBS is repeated every 10 s (Cole et al., 2022).

In the iTBS combined with olfactory stimulation group, pleasant odorants will be delivered through passive diffusers placed in the room dedicated to the iTBS protocol, during the 9min40 treatment. During the inclusion phase, from the 20 odorants presented in a hedonic olfactory test, 10 are considered as potentially diffusible during the treatment for two reasons: (1) they are known to be pleasant, (2) we have tested them so that they diffuse well and retain their pleasant odorant properties. Of these 10, 5 are single molecules known to be pleasant (Chalençon et al., 2022; Sezille et al., 2014) and 5 are blended odorants that are appreciated as much as single molecule odorants (Chen et al., 2022). The 3 highest rated odorants will be selected, and one will be randomly chosen and diffused at 20 Pa during each iTBS session using a heat diffusion system.

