##### 1.2.2.4 Olfactory anhedonia

Finally, our last objective will be to better characterize olfactory anhedonia (i.e., the impaired olfactory perception of pleasant odorants) by investigating its association with physical and social anhedonia, but also with early trauma. Olfactory anhedonia will be assessed before, immediately after treatment, after 1-month and 3-month follow-up through specific testing.

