#### 2.4.4 Olfactory anhedonia

Olfactory anhedonia will be assessed using an olfactory test in which the hedonic value of odorants will be evaluated before and after the treatment, as well as at 1 and 3 months after the treatment, and compared between the two groups. The relationship between olfactory anhedonia and physical and social anhedonia will be investigated, as well as its association with early life adversity.

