##### 4.2.1.6 Olfactory anhedonia

In addition, an olfactory hedonic judgment test will be assessed. It consists of the presentation of 20 odorants (with different hedonic value, from pleasant to unpleasant), 15 of which are monomolecular at a concentration of 20 Pa: isoamyl acetate, 2-phenylethanol, benzaldehyde, L-carvone, linalool, trans-anethol, benzyl-acetate, eucalyptol, cis-3-hexanol, citronellol, D-limonene, eugenol, n-caproic acid, trimethylamine, butyric acid, thioglycolic acid, and 5 are blended odorants: lemon/sweet orange/rosemary/bergamot/bitter orange/tree leaf/lavender/clary sage, linalool/d-limonene/linalyl acetate/beta-caryophyllene/beta-pinene/citral/geraniol/alphapinene/ eucalyptol/l-beta-bisabolene/menthone/geranyl acetate/2,6-dimethyl-5-heptenal/terpinolene, sweet orange/lavender/rosemary/bergamot/basil, vanilla extract/orange/ylang-ylang, and ylang-ylang/palmarosa/sweet orange/isoeugenol.

Participants will be allowed to freely smell each odorant presented in a randomized order. Then, participants will be asked to rate each odorant in terms of liking (“Is the smell pleasant?”), wanting (“Do you want to smell it again?”), intensity (“Is the smell intense?”), familiarity (“Is the smell familiar?”) (Chalençon et al., 2022). Each odorant will be rated on an analog scale ranging from 1 to 9 (1 for “Not at all,” 5 for “Neutral,” and 9 for “Extremely”).

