##### 4.4.1.2 Clinical data analysis

The proportion of remissions and responses will be investigated using chi-squared tests or Fisher's exact test. Changes in scores of depression severity, anhedonia and olfactory capabilities over the study period within the two groups will be analyzed using a mixed 2-way repeated measures ANOVA (GROUP^*^TIME) or a generalized linear mixed model depending on the distribution of the data. Pearson correlations will be performed to examine the relationship between olfactory anhedonia and pre-treatment physical and social anhedonia, as well as the relationship between childhood trauma severity and response to treatment, the relationship between childhood trauma severity and anhedonia (physical, social, and olfactory), and the relationship between childhood trauma severity and depression severity. Type of medication and type of depression (unipolar vs. bipolar) will be included in the analysis. We did not expect differences in response between patients with unipolar and bipolar depression.

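### Each combined-arm patient's three diffused odorants are also items of the hedonic test that compares the arms, so a pooled score would not show whether a difference is confined to those three; Table 1 also omits the follow-up hedonic tests

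*Protocol article*

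**What the plan says.** **Intervention.** Section 2.3 of the protocol article states that "from the 20 odorants presented in a hedonic olfactory test, 10 are considered as potentially diffusible during the treatment". It continues: "The 3 highest rated odorants will be selected, and one will be randomly chosen and diffused at 20 Pa during each iTBS session". Only the combined arm receives odorants. There are 50 sessions of 9 min 40 s.

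**Outcome.** Section 4.2.1.6 describes the only hedonic test in the article: "It consists of the presentation of 20 odorants (with different hedonic value, from pleasant to unpleasant), 15 of which are monomolecular". On scoring it says: "Then, participants will be asked to rate each odorant in terms of liking", and it adds wanting, intensity and familiarity, each from 1 to 9. Section 9 describes the odorant list as fixed. Section 1.2.2.4 defines olfactory anhedonia as "the impaired olfactory perception of pleasant odorants". Section 2.4.4 has the hedonic value of odorants measured before and after treatment, "as well as at 1 and 3 months after the treatment, and compared between the two groups".

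**Analysis.** Section 4.4.1.2 says: "Changes in scores of depression severity, anhedonia and olfactory capabilities over the study period within the two groups will be analyzed" with a GROUP by TIME model. It does not separate diffused from non-diffused odorants.

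**Schedule.** In Table 1 (section 2.5), the row for the ETOC and hedonic perception is marked for patients at week 0 only.

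**The concern.** The intervention and the outcome share stimuli. By the post-treatment test, a combined-arm patient has met three of the rated odorants again and again during treatment, and a patient on iTBS alone has not. Repeated exposure could plausibly raise ratings of those odorants (familiarity) or lower them (satiation).

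If only those three move, a pooled score moves with them. The result could then be reported as improved or worsened olfactory anhedonia, although the patient's pleasure in other pleasant smells has not changed. Section 1.2.2.4 defines the construct by pleasant odorants as a class, so the distinction matters for interpretation.

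Section 9 counts the choice of the three best-liked odorants as methodological control, but for earlier sensory exposure. It does not address this overlap.

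The Table 1 entry is a separate matter. If a site followed it literally, the outcome of sections 1.2.2.4 and 2.4.4 would not be measured in patients after baseline.

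**Working it through.** The article states no figure on this point, so there is none to reproduce.

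**Overlap and exposure (from sections 2.3 and 4.2.1.6)**
- Share of items exposed: 3/20 = 15% of the whole test; 3/10 = 30% if only the 10 candidates are scored. The article does not fix which items enter the score.
- Expected exposure per diffused odorant: 50/3 = 16.7 sessions, and 16.7 × 9.667 min = 161 min, against none in the other arm.

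**Effect on a pooled mean**

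Assumptions, not from the article: a shift confined to the three items, and an SD of change in the mean score of 0.7, 1.0 or 1.5 points. The number per arm is 37, from section 2.6.1.

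- SE of the arm difference = SD × √(2/37) = 0.163, 0.232, 0.349.
- Arm difference = (3/k) × shift, where k is the number of items scored.
- Chance of p < 0.05 = P(|Z + difference/SE| > 1.96).

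| Items scored | Shift on the 3 items | Difference in mean | Chance of p < 0.05 (SD 0.7 / 1.0 / 1.5) |
|---|---|---|---|
| 20 | 1.0 | 0.15 | 15% / 10% / 7% |
| 20 | 0.5 | 0.075 | 7.5% / 6.2% / 5.5% |
| 10 | 1.0 | 0.30 | 45% / 25% / 14% |
| 10 | 0.5 | 0.15 | 15% / 10% / 7% |

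With 40 per arm, the first row becomes 16% / 10% / 7%.

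**Would a split tell the two readings apart?**

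An item-level simulation used 3,000 runs and 37 per arm, with ratings rounded and limited to 1–9. Assumed means were 6 for candidates and 4 for the rest. Assumed SDs were 1.0 (person), 1.2 (item), 1.2 (error) and 0.8 (person-level change). The top 3 were defined at baseline in both arms.

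| Scenario | 20 items | 10 candidates | Other 7 | Top 3 |
|---|---|---|---|---|
| No shift | 4.6% | 4.6% | 4.5% | 5.2% |
| +1 on the top 3 only | 9.7% | 21.5% | 5.5% | 89.3% |
| −1 on the top 3 only | 10.9% | 24.4% | 4.9% | 91.6% |
| +0.5 on the top 3 only | 5.9% | 9.5% | 5.1% | 38.0% |
| +0.5 on every item | 66.0% | 57.2% | 53.2% | 38.1% |

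Entries are the percentage of runs with p < 0.05. In the second row the mean differences are 0.79 (top 3) and 0.00 (other 7). In the last row they are 0.42 and 0.47. The split therefore separates a confined change from a general one.

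**Are the other 7 unexposed?**

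Not strictly. The blends share ingredients, as the end of the list shows: "sweet orange/lavender/rosemary/bergamot/basil, vanilla extract/orange/ylang-ylang, and ylang-ylang/palmarosa/sweet orange/isoeugenol". From the full list:
- blends 1 and 3 share sweet orange, lavender, rosemary and bergamot;
- blend 5 shares sweet orange with blends 1 and 3, and ylang-ylang with blend 4;
- blend 2 contains linalool, d-limonene and eucalyptol, which are also single items.

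The article does not name the 5 single-molecule candidates, so 0 to 3 of those molecules were allowed among them. Over all C(10,3) = 120 top-3 sets, taken as equally likely, 83% to 100% leave at least one of the 7 that shares a component with a diffused odorant. The average is 1.6 to 2.8 of the 7. If such items took 25% or 50% of a 1-point shift (on average 2.3 of the 7 affected), the 7-item difference would be 0.08 or 0.16, significant in 6% or 10% of runs.

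**Precision of the 7-item score**

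SE ratio against 10 items = √{[r + (1−r)/7] / [r + (1−r)/10]}, where r is the assumed inter-item correlation of change. For r = 0.1, 0.3 and 0.5 it is 1.097, 1.040 and 1.019.

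**Schedule**

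Sections 1.2.2.4 and 2.4.4 require four time points. In Table 1's weeks these are 0, 2, 6 and 14. The table marks one of the four.

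**The case against.** The strongest reply is that exposure to odorants is the treatment. A change in the ratings of treated odorants is then part of its effect, and randomisation makes the arm comparison valid. That stands. A reader might infer that the comparison is biased, or that a difference could never be attributed to a general change. The documents do not support either reading. Each odorant is rated individually, in both arms, so the ratings that section 2.4.4 calls for are enough to separate the two explanations.

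A second reply is that scoring details belong in an analysis plan that is not shown. This also has weight: section 4.4.1.2 neither prescribes a pooled score nor forbids an item-level one. The absence of a scoring rule is therefore not the point. The point is that the article's own definitions of treatment and outcome create the overlap, and that the one section discussing the odorant selection as a control (section 9) does not mention it.

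Third, the magnitudes rest wholly on assumptions, and most are small on the 20-item mean. The 45% figure needs a 10-item score, the smallest SD and a full-point shift together. This is correct, and no figure here should be read as an expected false-positive rate.

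Finally, the Table 1 gap may be a simple omission. The table also leaves out the free-viewing task after sessions 1 and 5 and the apathy scale at 1 and 3 months, both stated in the text. That is plausible, and it is a reason to correct the table. It adds no weight to the overlap.

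**Conclusion.** The concern holds as a limit on interpreting one secondary outcome. The overlap of three items per patient is documented: 15% of the test, or 30% of the candidates. The GROUP by TIME comparison estimates a valid effect of assignment, but a pooled score alone would not show whether that effect extends beyond the exposed odorants.

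How far exposure would move ratings, and in which direction, is unknown. Under the assumed shifts of 0.5 to 1 point and SDs of 0.7 to 1.5, the chance that the three items alone give a significant difference runs from 5.5% to 15% on 20 items and from 7% to 45% on 10.

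The contradiction between Table 1 and sections 1.2.2.4 and 2.4.4 is definite and needs correcting in its own right. The primary remission endpoint and the correlations at baseline are not affected.

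**What to change.** 1. Keep the overall between-arm comparison in sections 2.4.4 and 4.4.1.2. Add a pre-specified supportive split on the liking rating. Define each patient's top 3 of the 10 candidates from baseline liking, by the same rule (including ties) in both arms. Report the arm contrast for (a) the remaining 7 candidates and (b) the top 3. Describe (a) as reduced-exposure, not unexposed, because the blends share components. Section 2.3 should say that the highest-rated odorants are those with the highest liking, so that (b) matches what was diffused.
2. Read only the between-arm contrasts. Selecting the top 3 at baseline causes regression to the mean within each part, which is equal in expectation across arms under a common rule.
3. Fix the split before the interim analysis at 40 patients, because section 5.1.2 repeats the secondary analyses there.
4. Correct Table 1 so that patients take the hedonic test at weeks 2, 6 and 14 as well as week 0.
5. As a clerical correction, reconcile section 4.2.1.6, which states 15 single molecules and names 16.

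**Cost.** No patient, test or visit is needed beyond what sections 1.2.2.4 and 2.4.4 already require. The standard error of (a) is about 2% to 10% larger than for all 10 candidates. Each part has less power than the whole: for a uniform 0.5-point change in the simulation, 53% for (a) and 38% for (b), against 57% for the 10 candidates and 66% for all 20 items. There is one more supportive comparison to report, and it should be labelled as such.

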### 2.4 Outcomes

#### 2.4.1 Primary outcome

The primary outcome is the number of patients meeting remission criteria within each post-treatment group. Remission is defined as a MADRS score of 10 or less (Zimmerman et al., 2004) on a scale of 0–60, assessed at the end of 50 iTBS sessions.

#### 2.4.2 Other clinical and behavioral outcomes

Several clinical and behavioral features will be assessed using:

- the 10-item MADRS total scores to assess depression severity.- the number of responders, defined as those who show a reduction of at least 50% in their MADRS score.- the 13-item Beck Depression Inventory (BDI) (Gould, 1982), to assess self-rated depression.- the 11-item Young Mania Rating Scale (YMRS) (Young et al., 1978), to assess manic states.- the Childhood Trauma Questionnaire (CTQ) (Bernstein et al., 2003) to study early life adversity.- the Chapman Social Anhedonia Scale and the Chapman Physical Anhedonia Scale (Chapman et al., 1976) to investigate respectively physical and social anhedonia.- the Snaith-Hamilton Pleasure Scale (SHAPS) (Snaith et al., 1995) to assess global anhedonia.- the Apathy Evaluation Scale (AES) (Marin et al., 1991) to assess apathy.- the Free-Viewing task (FVT) to assess cognitive biases, more precisely, early and sustained emotional attentional biases.

These outcomes will be assessed before and after the 50 iTBS sessions. The same outcomes will also be assessed at 1 and 3 months after treatment and compared between the two groups. In addition, the relationship between early life adversity and depression severity will be examined, as well as its association with the evolution of depressive symptoms and especially anhedonia.

#### 2.4.3 Neurobiological outcomes

The brain connectivity and activity within the brain regions involved in the reward and olfactory circuitry we will be explored through functional Magnetic Resonance Imaging (fMRI) and dual-site transcranial magnetic stimulation protocol. This will be assessed before and after the treatment, and compared between the two groups. The relationship between changes in neurobiological outcomes and changes in clinical features will be also investigated.

#### 2.4.4 Olfactory anhedonia

Olfactory anhedonia will be assessed using an olfactory test in which the hedonic value of odorants will be evaluated before and after the treatment, as well as at 1 and 3 months after the treatment, and compared between the two groups. The relationship between olfactory anhedonia and physical and social anhedonia will be investigated, as well as its association with early life adversity.

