#### 1.2.2 Secondary objectives

##### 1.2.2.1 Clinical outcomes

We will assess the acute and long-term effects of the treatment on several clinical features of MDD: remission (MADRS_10_ < 10) and response (reduction of at least 50% in MADRS_10_ score), severity of self-rated depression (BDI_13_), physical and social anhedonia and apathy immediately after the treatment, after 1-month and 3-month follow-up.

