### 2.2 Eligibility criteria

#### 2.2.1 Patients with MDD

To be eligible for the study, patients must meet the following criteria: be 18 years or older, have a primary diagnosis of single or recurrent non-psychotic major depressive disorder (unipolar or bipolar) episode according to the Diagnostic and Statistical Manual of Mental Disorders, fifth edition (DSM-5) criteria, scored 20 or more on the 10-item Montgomery and Asberg Depressive Rating Scale (MADRS) (Montgomery and Åsberg, 1979) and scored higher than 2 on the MADRS anhedonia score (item #8). All patients should be able to speak and read French, and sign a written informed consent.

Patients with unipolar depression should be on stable antidepressant medication for at least 4 weeks prior to inclusion with no mood changes (after at least one previous treatment failure). Patients recruited for this study had a treatment-resistant depressive episode, defined as failure to respond to at least two antidepressant regimens despite adequate dosage, duration and adherence to treatment (McIntyre et al., 2023). Patients will remain on the same stable antidepressant medication throughout the trial without any changes. Benzodiazepines are not allowed.

Patients with bipolar depression should have treatment-resistant bipolar depression at enrolment, despite optimized mood-stabilizing treatment of adequate duration and dosage (for at least one month). Throughout the study period, patients will be on stable mono- or bi- therapy with mood stabilizers, without antidepressants or benzodiazepines (Bulteau et al., 2019).

Augmentation strategy with antipsychotics is allowed.

Participants will be not eligible if they have: anosmia [as verified by the European Test of Olfactory Capabilities (ETOC) (Thomas-Danguin et al., 2003)], whether congenital, or due to upper respiratory tract infection, nasal and/or sinus disease, brain injury or nasal surgery; neurological disorders; concurrent comorbid psychiatric disorders or substance abuse (except tobacco); contraindications to TMS (implanted medical devices or metallic foreign body in the head); contraindications to MRI; history of non-response to treatments based on sensory stimulation or rTMS; pregnant or breastfeeding mothers (controlled by urine pregnancy tests); a conservatorship or guardianship order.

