**Assessments:**							
MADRS	**X**	**X**		**X**	**X**	**X**	
BDI		**X**		**X**	**X**	**X**	**X**
CTQ		**X**					**X**
Chapman scales		**X**		**X**	**X**	**X**	
SHAPS		**X**		**X**	**X**	**X**	**X**
AES		**X**		**X**			**X**
ETOC/hedonic perception		**X**					**X**
FVT		**X**		**X**			
MRI		**X**		**X**			
Dual-site TMS		**X**		**X**			**X**

iTBS, intermittent Theta Burst Stimulation; MDD, Major Depressive Disorder; MADRS, Montgomery and Asberg Depressive Rating Scale; BDI, Beck Depression Inventory; CTQ, Childhood Trauma Questionnaire; SHAPS, Snaith-Hamilton Pleasure Scale; AES, Apathy Evaluation Scale; ETOC, European Test of Olfactory Capabilities; FVT, Free-Viewing Task; MRI, Magnetic Resonance Imagery; TMS, Transcranial Magnetic Stimulation.

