#### 4.2.2 Behavioral assessment

##### 4.2.2.1 Eye tracking free-viewing task

The Free Viewing Task (FVT) will assess attentional emotional bias before the treatment and after 1, 5, and 50 rTMS sessions, as it correlates with depression severity (Imbert et al., 2024). This makes it a relevant outcome to evaluate before and after treatment, providing objective measures of improvement. In the task, pairs of faces: one emotional (happy or sad) and one neutral, are presented randomly for 3,500 ms to the right and left of a fixation cross. The inter-stimulus interval is randomized among 1,250, 1,500, or 1,750 ms, and the next pair appears only when the participant fixates on the cross. A total of 32 pairs (16 happy- neutral, 16 sad-neutral pairs), with 16 different identities (8 males, 8 females), will be presented. The faces are extracted from the FACES database (Ebner et al., 2010).

Throughout the task, gaze position and eye movements are recorded using an eye-tracking system (SMI SensoMotoric Instruments with BeGaze 3.6.52, Teltow, Germany).

We will assess early and sustained attention allocation using eye-movement recordings. Sustained attention will be measured by dwell time (DT), the total time spent fixating on faces. The emotional bias score will be the difference between DTs for emotional and neutral faces. Early attention will be measured by the orientation of the first saccade, the first face the participant looks at. The laterality quotient will be the difference between the number of first saccades to emotional vs. neutral faces, divided by the total trials. Positive values indicate a bias toward emotional faces; negative values indicate a bias toward neutral faces.

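### Table 1 conflicts with the text on when four secondary-outcome instruments are given: the hedonic olfactory test, AES, free-viewing task and YMRS

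*Protocol article*

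**What the plan says.** All references are to the protocol article.

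- **Hedonic olfactory test.** The objective in 1.2.2.4 states: "Olfactory anhedonia will be assessed before, immediately after treatment, after 1-month and 3-month follow-up through specific testing". Section 2.4.4 repeats this: "the hedonic value of odorants will be evaluated before and after the treatment, as well as at 1 and 3 months after the treatment", with a comparison between the two groups.
- **Apathy (AES).** Section 1.2.2.1 plans to assess "physical and social anhedonia and apathy immediately after the treatment, after 1-month and 3-month follow-up".
- **Free-viewing task (FVT).** Section 4.2.2.1 places it "before the treatment and after 1, 5, and 50 rTMS sessions", and the objective in 1.2.2.2 gives the same four time points.
- **YMRS.** Section 2.4.2 lists "the 11-item Young Mania Rating Scale (YMRS") among the outcomes, and 4.2.1.1 describes its scoring.
- **General follow-up rule.** After listing its outcomes and a pre/post assessment, 2.4.2 adds: "The same outcomes will also be assessed at 1 and 3 months after treatment and compared between the two groups".
- **Table 1 (section 2.5).** This is the only visit schedule given. One row, "ETOC/hedonic perception", covers both olfactory tests. For patients it is marked at week 0 and nowhere else. AES and FVT are each marked at weeks 0 and 2. YMRS has neither a row nor an entry in the abbreviation list.
- **Analysis.** Section 4.4.1.2 plans a GROUP by TIME analysis of change in depression severity, anhedonia and olfactory capabilities.

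**The concern.** The text and the schedule cannot both be followed for these four instruments. Whoever runs the visits from Table 1 would omit measurements that the objectives and outcome sections promise. Ratings that are not taken at the planned visit cannot be recovered later.

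The olfactory test matters most. Pleasant odour is the experimental component of the trial, and olfactory anhedonia is a named objective with a between-group comparison over time. With one patient time point there is no change score and no GROUP by TIME term. The carry-forward rule in 4.4.2 would not help, because carrying week 0 forward gives a change of zero for every patient. For YMRS there would be no data at all, in a trial that also enrols patients with bipolar depression. Section 5.1.2 repeats the secondary analyses at the interim look after 40 patients, so the gap would show there first.

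**Working it through.** The plan gives no figure to reproduce here. The check sets the stated time points beside the marked cells.

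**Step 1: is the table read correctly?** The header has seven columns: weeks -1, 0, 1, 2, 6 and 14, and the healthy-volunteer visit. Each of the nine assessment rows checked (MADRS, BDI, CTQ, Chapman, SHAPS, AES, ETOC/hedonic perception, FVT, MRI) splits into exactly seven cells. The blanks are therefore not a shift from reading the PDF. MADRS, BDI, Chapman and SHAPS are each marked at weeks 0, 2, 6 and 14, so the table does show follow-up for some scales.

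**Step 2: map the text to weeks.** Treatment takes two working weeks, so post-treatment is week 2, one month later is week 6 (2 + 4) and three months later is week 14 (2 + 12). With five sessions per working day (section 2.3), sessions 1 and 5 both fall on the first treatment day. The FVT has no mark in the week 1 column.

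**Step 3: compare (patients only).**

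| Instrument | Time points in the text | Source | Marked in Table 1 | Missing |
|---|---|---|---|---|
| Hedonic test | weeks 0, 2, 6, 14 | 1.2.2.4, 2.4.4 | week 0 | 4 - 1 = 3 of 4 |
| AES | weeks 0, 2, 6, 14 | 1.2.2.1, 2.4.2 | weeks 0, 2 | 4 - 2 = 2 of 4 |
| FVT | baseline, after sessions 1, 5 and 50 | 1.2.2.2, 4.2.2.1 | weeks 0, 2 | 4 - 2 = 2 of 4 |
| YMRS | weeks 0, 2, 6, 14 | 2.4.2 | none | 4 - 0 = 4 of 4 |
| MADRS (primary) | week 2, plus baseline and follow-up | 2.4.1, 2.4.2 | weeks -1, 0, 2, 6, 14 | none |

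**Step 4: what each gap removes if the table is followed.**

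- Hedonic test: all change over time and the between-group comparison in 2.4.4. The baseline correlations in 4.4.1.2 (olfactory anhedonia with pre-treatment physical and social anhedonia, and with childhood trauma) need only week 0 and survive.
- YMRS: all data.
- AES: the 1- and 3-month comparisons. Week 0 versus week 2 survives.
- FVT: the early-change comparison. Week 0 versus week 2 survives.

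**Step 5: two related loose ends.**

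- Section 4.4.1.2 analyses change in olfactory capabilities, which 4.2.1.5 measures with the ETOC. No section says that the ETOC is repeated after treatment. It is a different test from the hedonic one, although they share a row.
- The ETOC decides an exclusion ("anosmia [as verified by the European Test of Olfactory Capabilities (ETOC")), and 2.3 places the hedonic test in the inclusion phase. Table 1 puts both in the allocation column (week 0), not the inclusion column (week -1).

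**The case against.** The best defence is that the harm is conditional. Section 2.5 presents Table 1 as an overview, the trial has one centre, and the text gives the olfactory timing twice and the FVT timing twice. Staff who read the text would collect the data. That is fair, and it is why the consequences are stated only for the case where the table is followed. It does not remove the conflict. No other schedule is given, and 7.3 describes the article as the full protocol. An analysis plan cannot supply measurements that were never taken.

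Several stronger readings are tempting, and the documents do not support them:

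- **That these outcomes become impossible to analyse.** This is true of olfactory change and of YMRS. It is not true of AES and FVT, which keep their pre/post comparison. Section 4.4.1.2 also names no specific analysis of YMRS or apathy.
- **That mania will never be measured.** Sections 2.4.2 and 4.2.1.1 both commit to the YMRS. Only the schedule omits it.
- **That anosmic patients could be randomised.** The table shows only a column mismatch. Week 0 also holds other baseline measures, there is an eligibility screen at week -1, and nothing says that the ETOC follows randomisation.
- **That the FVT lacks 4 of 6 time points.** That count adds 1 and 3 months from the general sentence in 2.4.2. Read literally, the sentence also covers the CTQ, a childhood history, so it is loosely drafted. The two FVT-specific sections support 2 of 4.

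It is also fair to say that the text need not be right everywhere. For AES and the early FVT, the documents do not show whether the text or the table reflects the intention.

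**Conclusion.** The inconsistency is real and should be fixed. It affects secondary outcomes only. A reader might infer that the main result is at risk, but it is not: the MADRS is marked at every time point it needs, so remission, response and depression severity are fully scheduled. The same holds for self-rated depression and for physical, social and global anhedonia.

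In patients, Table 1 omits 3 of 4 hedonic-test time points, 2 of 4 for AES, 2 of 4 for FVT and all 4 for YMRS. If the table were followed for all 80 patients, the longitudinal part of objective 1.2.2.4 and the YMRS outcome would be lost. AES and FVT would lose only the missing time points.

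This rests on two assumptions: that Table 1 is the working schedule, and that the text's 1 and 3 months are the week 6 and week 14 visits. The direct reading of the table supports the second.

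**What to change.** Reconcile Table 1 with the text before further data are collected:

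1. Mark the hedonic olfactory test at weeks 0, 2, 6 and 14, in a row separate from the ETOC.
2. Add AES at weeks 6 and 14 and FVT after sessions 1 and 5, or amend the objectives and outcome sections to match the table.
3. Add a YMRS row at the time points in 2.4.2.
4. State whether the ETOC is repeated after treatment. If it is not, remove olfactory capabilities from the change analysis in 4.4.1.2.
5. Reconcile the week 0 column for the ETOC and hedonic test with the eligibility role of the ETOC in 2.2.1 and the inclusion-phase wording in 2.3.
6. Restrict the general follow-up sentence in 2.4.2 to the scales meant to be repeated. This excludes the CTQ, and the sentence should say whether FVT is included.

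The cost is a corrected table and a few sentences, plus some assessment time. The largest item is the hedonic test: 20 odorants with 4 ratings each is 20 × 4 = 80 ratings per visit, at three further visits that already exist. The article gives no durations, so the added minutes cannot be stated. The two early FVT runs would fall on the first treatment day.
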